## Abstract

**Background:**

Previous trials in Africa and Asia, including Bangladesh, showed that community health workers can effectively treat young infants (7–59 days) with fast breathing and children (2–59 months) with chest indrawing pneumonia at home with oral amoxicillin using enhanced integrated community case management (iCCM) protocols. However, the Enhanced Management of Pneumonia in Community (EMPIC), its pneumonia-specific component, has not yet been applied in routine government health systems. Here, we developed a protocol for a feasibility study on the integration of EMPIC into community clinics in Bangladesh through existing government health systems.

**Methods:**

This study will adopt an implementation research approach that integrates quantitative and qualitative methods. A delivery package will be co-developed with stakeholders to introduce enhanced pneumonia management through government systems in three phases within community clinics of selected *upazilas* in Kushtia and Dinajpur districts. We will use the plan-do-check-act cycle framework to evaluate implementation, track progress, identify gaps, and test potential solutions. Data collection methods will include health facility assessments, data extractions from routine registers and monthly reports, household surveys, and community follow-ups of under-five children with pneumonia on days 7 and 14 post-treatment. The primary outcome is high (*i.e.* ≥80%) and effective coverage (*i.e.* patients receiving the full course of pneumonia treatment) of pneumonia treatment in under-five children. Secondary outcomes include treatment failure rates among under-five children with pneumonia; availability of commodities and supplies for pneumonia management; health worker knowledge, caregiver awareness and care-seeking practices regarding childhood pneumonia; pneumonia prevalence among under-five children; community clinic utilisation for pneumonia-related symptoms by under-five children; and treatment compliance.

**Conclusions:**

Our findings may inform the evidence-based scale-up of enhanced pneumonia management in Bangladesh and other low- and middle-income countries, contributing to improved community-level management of childhood pneumonia.

Despite progress in reducing child mortality over the past two decades, global efforts fell short of achieving the Millennium Development Goal 4 target of reducing under-five mortality by two-thirds from 1990 to 2015 [1]. Despite further drops in the global under-five mortality rate by 2020 [1], an estimated 4.8 million were recorded among this population in 2023, translating to 13 100 deaths a day [2].

Pneumonia accounts for approximately 14% of deaths among children under five years of age, making it the leading cause of death in this group [3]. In 2019, there were 45 million cases of pneumonia globally among children under five years old, resulting in over 700 000 deaths. However, the burden and mortality of childhood pneumonia are unevenly distributed worldwide: sub-Saharan Africa, for example, has twice the incidence and 60 times the mortality of high-income countries [4]. Accelerated efforts are needed to avert pneumonia-related deaths to achieve the highly ambitious Sustainable Development Goal (SDG) target of reducing under-five mortality to below 25 per thousand live births [5].

In Bangladesh, pneumonia accounted for around 24% of all under-five deaths in 2022, with a mortality rate of 7 per 1000 live births [6]. Despite a high coverage of *Haemophilus influenzae* type b and pneumococcal conjugate vaccines (98–99%), only 46% of children with suspected pneumonia are taken to an appropriate healthcare provider [7]. In 2022, the country’s median integrated Global Action Plan for Pneumonia and Diarrhoea score was 68% overall and 81% for pneumonia specifically, falling short of the global target of 84% [7]. The care-seeking behaviour of its population is influenced by factors such as caregivers' knowledge, parental joint decision-making, mistrust of the healthcare system, faith in traditional care, spiritual beliefs, distance to health facilities, shortage of qualified staff, and household wealth [8–10]. Many children with pneumonia symptoms are taken to private sector providers, with only a small percentage seeking care from public health facilities [6]. The gaps in achieving high coverage of core interventions and the reliance on inappropriate care-seeking practices highlight the need for improved community-level pneumonia management in Bangladesh.

Global recommendations for low-resource settings indicate the adoption of the Integrated Management of Childhood Illness (IMCI) strategy for outpatient management of common childhood illnesses, including pneumonia. Developed by the World Health Organization (WHO) and the United Nations Children’s Fund (UNICEF) in the mid-1990s, the IMCI strategy promotes accurate identification of childhood illnesses in outpatient settings, appropriate combined treatment of all major illnesses, strengthened counselling of caretakers, and provision of preventive services [11–13]. It also emphasises the need for speeding up the referral of severely ill children and improving the quality of care at the referral level [11,13–15]. In home settings, it promotes appropriate care-seeking behaviours, improved nutrition, preventive care, and correct implementation of prescribed care [11,13–15].

Effective implementation of IMCI has led to increased use of health services, improved health workers' performance and quality of care, reduced irrational use of drugs, and a decline in under-five mortality rates in countries with limited resources [16–24]. The approach is now implemented in more than 100 countries, with 81% reporting full implementation of all three components, and approximately half reporting adoption in 90% or more districts [15,25]. Despite the high reported implementation, IMCI has yet to benefit children most in need, as coverage remains lowest in high-mortality settings, as do gaps in availability, accessibility, and quality of services for pneumonia management [7,15,26]. Achieving the 2025 target of ending preventable pneumonia deaths and the 2030 SDG target of reducing neonatal mortality to 12 or fewer per 1000 live births will be challenging without revitalised strategic focus, substantial investments, and concerted efforts across the global health community [5,7].

Bangladesh was one of the five countries targeted by the WHO-led Multi-Country Evaluation of IMCI Effectiveness, Cost, and Impact study [27]. In its last two years, the mortality rate was 13.4% lower in IMCI intervention areas compared to comparison areas [17]. The study also reported that successful implementation of the IMCI package led to improved health worker skills, health system support, and family and community practices, translating into increased care-seeking for illnesses [17]. It also demonstrated a positive effect on exclusive breastfeeding and stunting [17]. Based on the experience gained and evidence generated through this study and global recommendations, the Government of Bangladesh adopted the IMCI strategy in 1998. After successful piloting of facility-based IMCI in three sub-districts (*upazillas*), IMCI was included in the Sector Investment Plan of the Health, Nutrition, and Population Sector Programme 2005–2010 as one of the priority strategic components to improve child health in Bangladesh. Currently, facility-based IMCI has been scaled up across the country.

Addressing the high burden of childhood pneumonia in Bangladesh, however, requires further expanding the coverage of IMCI services and hospital inpatient care. The current service delivery model, starting at union-level facilities (health centres), is inadequate, with less than 50% coverage [7]. To improve this, services need to be extended to community clinics (CCs) at the ward/village level, each serving 6000–10 000 people. As of June 2020, over 13 812 CCs have been established and made functional, staffed by community healthcare providers (CHCPs) with basic training [28].

Evidence from multi-country trials in Ethiopia, Malawi, Bangladesh, and India shows that community-based management of pneumonia with oral amoxicillin is as effective as hospital referrals, with treatment failure rates being equivalent and deaths observed in less than 1% of cases [29,30]. Effective pneumonia treatment requires early case identification, prompt treatment close to home, well-trained providers, necessary supplies, and efficient referral systems. High non-compliance with referral advice in LMICs underscores the need for community-based management [7,20,21,31–33].

Implementing revised pneumonia management guidelines [34] in CCs can reduce the need for referrals, decrease costs and save time. Assessing the feasibility of this approach in real-life settings is crucial before scaling up. This will help improve pneumonia treatment in areas where access to referral facilities is limited, enhancing coverage and effectiveness and ultimately reducing childhood pneumonia burden. Therefore, through an implementation research approach, we aim to introduce Enhanced Management of Pneumonia in Community Clinics (EMPIC) through the government health systems and structures in Bangladesh to increase effective population-based coverage of pneumonia treatment in under-five children and scale-up.

## METHODS

The goal of this study is to achieve high and effective population coverage of pneumonia treatment in under-five children in Bangladesh and to develop a scalable implementation strategy for contextual adaptation to other low- and middle-income countries (LMICs).

Our primary objective is to increase access to pneumonia treatment in under-five children to achieve high (≥80%) and effective population-based coverage (*i.e.*, patients receiving the full course of pneumonia treatment) in the study area. We also set five secondary objectives:

to increase care-seeking practices from appropriate healthcare providers for general danger signs and pneumonia-related signs of under-five children;to determine the rate of clinical treatment failure of young infants 7–59 days old with fast breathing and children 2–59 months old with fast breathing and/or chest indrawing pneumonia who received treatment from CHCPs;to assess the compliance with pneumonia treatment among young infants 7–59 days old with fast breathing and children 2–59 months old with fast breathing and/or chest indrawing pneumonia who received treatment from CHCPs;to explore the knowledge, perceptions, and experiences of health facility staff, CHCPs, and beneficiaries on the implementation of pneumonia management;to improve the availability of essential commodities in the CCs to manage pneumonia in under-five children.

We will achieve these objectives through three activities: designing an implementation delivery package for introducing the EMPIC in Bangladesh (activity 1); employing a continuous learning process during the implementation period to understand the prerequisites for the scale-up of the package (activity 2); and assessing whether the implementation delivery package worked by documenting the implementation process, understanding and assessing care practices, and exploring the experiences of health managers, health service providers, and caregivers related to the implementation of the package (activity 3).

### Study design

This study will use an implementation research approach, incorporating both quantitative and qualitative data collection methods. The design will be informed by evidence from a cluster-randomised non-inferiority trial conducted in several countries, including Bangladesh, which demonstrated that community-based treatment of young infants (7–59 days) with fast-breathing pneumonia by trained community health workers is both safe and effective, performing comparably to referral-based management [29,30]. Building upon these findings, this study focuses on evaluating the implementation outcomes in real-world health system contexts by integrating EMPIC within routine primary healthcare delivery systems.

### Study settings, period, and population

We will select two *upazilas* (sub-districts) in total: one each from the Kushtia and Dinajpur districts. From them, we will choose 20 CCs based on service availability and caseload, in consultation with national and district-level health managers. Dinajpur district covers an area of 3437.98 km^2^ and is home to 299 0128 inhabitants, resulting in a population density of 868 people per km^2^ [35]. The district has one medical college hospital, one district hospital, 12 *upazila* health complexes (sub-district hospitals), 119 union sub-centres and union health & family welfare centres (union level health centres), and 337 CCs (health outpost centres) [36]. Kushtia district has a population of 1 986 838 and covers an area of 1621.15 km^2^, leaving a density of 1073 people per km^2^ [37]. The district's health facilities include one district hospital (secondary level referral hospital), five *upazila* health complexes (sub-district hospitals), 73 union health and family welfare centres (union level health centres), and 205 CCs [36]. The study will be conducted across 24 months, where 18 months will be reserved for the delivery of the implementation package.

The study population will be under-five children presenting with pneumonia in CCs, CHCPs working in CCs, caregivers and family members of children visiting CCs, district and sub-district level health managers and supervisors and central-level health managers and policymakers.

### Data collection by activities

#### Activity 1

We propose to develop an implementation package for introducing EMPIC through consultation with key stakeholders in Bangladesh, including the National Newborn Health and IMCI Programme, the Community-based Healthcare Programme, and other development partners. The implementation package will be developed around the enhanced management of pneumonia strategy (**Figure 1**), where the integrated community case management (iCCM) strategy [34], recommended by the WHO for community health workers, will be modified and incorporated into the existing IMCI strategy [38] framework in Bangladesh. Under the enhanced strategy, under-five children presenting with any danger signs (severe pneumonia or very severe disease/critical illness), infants aged 0–6 days with fast breathing or possible serious bacterial infection, and infants aged 7–59 days with any danger sign (possible serious bacterial infection) will be directed to referral facilities. In addition, CHCPs will conduct pulse oximetry in children with cough and/or difficulty in breathing and refer hypoxaemia cases to referral facilities. In contrast, children aged 7–59 days with fast breathing pneumonia or aged 2–59 months with fast breathing and/or chest indrawing pneumonia will be treated with oral amoxicillin (**Box 1**).

**Figure 1 F1:**
[figure not shown]
Implementation plan for pneumonia management in community clinics. CHCP – community healthcare provider, EPI – Expanded Programme of Immunization.

Box 1Signs and classification of sick young infants and sick children, by different age groups, according to the IMCI Chart Booklet (Bangladesh) 2019 [38]0–59 daysPossible serious bacterial infection or very severe disease- critical illness
*Any one or more of the following signs: unconsciousness/drowsy, convulsion or H/O convulsion, unable to feed, persistent vomiting, bulging fontanelles, apnoea, central cyanosis, major bleeding, weight <1500 g, major congenital malformation, surgical condition requiring hospitalisation*
Possible serious bacterial infection or very severe disease – clinically severe infection*Any one or more of the following signs: severe chest indrawing, fever (37.5°C or above) or low body temperature (less than 35.5°C), not feeding well,*
*movement only when stimulated/no movement at all*Possible serious bacterial infection or very severe disease – fast breathing pneumonia (0–6 days)
*Fast breathing (60 breaths per minute or more) for age 0–6 days.*

*Fast breathing pneumonia (7–59 days).*

*Fast breathing (60 breaths per minute or more) for age 7–59 days.*

**2–59 months**
Severe pneumonia or very severe diseaseAny general danger signs: the child being unable to drink or be breastfed, vomiting everything, having convulsions, being lethargic or unconscious, and convulsing now, or stridor in a calm child, or oxygen saturation (SpO_2_) <90%PneumoniaChest indrawing or fast breathing (50 breaths per minute or more for age 2–12 months, 40 breaths per minute or more for age 12–59 months)

To ensure the safe and effective use of pulse oximetry within CCs, devices will undergo routine maintenance and calibration, and supplies of drugs and equipment will be coordinated through the Directorate General of Health Services logistics system. The CHCPs will receive periodic refresher training to maintain competency in pneumonia management, with an emphasis on rational antibiotic use and strict adherence to referral protocols. Antibiotic prescriptions and referral decisions will be regularly audited and monitored through routine follow-up visits, while plan-do-check-act (PDCA) cycles will enable identification and correction of any deviations in real time, collectively reducing the likelihood of over-treatment, inappropriate antibiotic use, or missed referrals. These operational safeguards, combined with the PDCA cycles for continuous learning and ongoing stakeholder engagement, will allow the programme to monitor and address potential challenges related to device function, supply reliability, and rational antibiotic use. Insights from the implementation activities will inform ongoing improvements to the programme model through the PDCA cycles in activity 2, ensuring continuous adaptation and context-specific improvements.

The intervention package will include activities aimed at increasing care-seeking practices for childhood illnesses at CCs. The first set of interventions will focus on raising knowledge and awareness among families and communities about the danger signs. The second set will aim to strengthen health systems and improve the quality of care for children with pneumonia at CCs. While these health system interventions are not directly linked to increasing demand, ensuring the availability, readiness, and quality of services is essential for enhancing care-seeking practices.

#### Activity 2

The logic model for enhanced pneumonia management in CCs will be finalised through consultations with key stakeholders, including national policymakers, clinical experts, and health managers. The IMCI programme will lead the implementation, using government systems without financial incentives for providers. The implementation research team (icddr,b) will support the IMCI programme and continuously update the package. An initial situation analysis in Kushtia and Dinajpur districts will inform updates to the programme model. The feasibility will be tested in three rounds using the PDCA cycle (**Figure 2**). Implementation findings will be reviewed in existing monthly sub-district health facility meetings with CHCPs in the study area, which will be chaired by an *upazila* health and family planning officer. These sessions, embedded in a formal governance platform, will track progress, identify gaps, and agree on corrective actions, ensuring accountability, while avoiding parallel structures. To monitor and mitigate potential increases in CHCP workloads, task feasibility workflow challenges, and adherence to the enhanced pneumonia protocol will be assessed through PDCA cycles and routine supervision. Feedback from CHCPs will inform minor adjustments or supportive measures to maintain protocol fidelity without compromising service delivery or sustainability. Stakeholders will be involved at every stage to ensure ownership and capacity development. These minor adjustments may be introduced in real time, while any substantive protocol changes will require prior institutional review board approval. Both qualitative and quantitative data will be collected by a dedicated research team.

**Figure 2 F2:**
[figure not shown]
Proposed plan-do-check-act cycle.

The EMPIC intervention is guided by a theory of change (**Figure 3**) that links CC-level pneumonia management to improved health outcomes. The framework outlines how key inputs, such as training, supervision, diagnostic tools, and community engagement, are expected to strengthen service delivery outputs, leading to improved treatment fidelity, care-seeking, and adoption of enhanced pneumonia management. These primary outcomes are anticipated to translate into greater coverage, integration within health systems, and, ultimately, reduced pneumonia-related morbidity and mortality among under-five children.

**Figure 3 F3:**
[figure not shown]
Theory of Change underpinning EMPIC intervention. CC - community clinic, CHCP – community healthcare provider, EMPIC - Enhanced Management of Pneumonia in Community, IMCI – Integrated Management of Childhood Illness, MoHFW – Ministry of Health and Family Welfare, PDCA – Plan-Do-Check-Act.

#### Activity 3

Health facility assessments will be conducted at baseline and end-line to evaluate the service availability and readiness of CCs, using structured tools to assess equipment, drugs, and logistics for pneumonia management, as well as CHCPs’ knowledge regarding management of childhood pneumonia. We will extract data from routine registers to evaluate recording and reporting practices, and will monitor monthly utilisation reports through central management information systems. Community follow-up of the pneumonia-classified children on the 7th and 14th days of CC visit will involve household visits by study-nurses to assess treatment failure rates and adherence to guidelines. Baseline and endline household surveys will measure caregivers' knowledge, care-seeking practices, and treatment outcomes, defining treatment failure based on specific clinical criteria.

We will explore the experiences of health managers, CHCPs, and caregivers through in-depth and key informant interviews which will focus on contextual factors, including social determinants of health, cultural beliefs, caregiver practices, and CHCPs and health system constraints (such as workload assessment) that influence care-seeking and treatment adherence. Insights from these interviews will inform iterative refinement of the intervention and interpretation of fidelity, acceptability, and adoption outcomes. This comprehensive data collection (**Table 1**) will inform continuous improvements in pneumonia management at CCs.

**Table 1 T1:** Data collection procedure throughout the study period

	Baseline	Q1	Q2	Q3	Q4	Q5	Q6	Endline
Health facility assessment	X	O	O	O	X	O	O	X
Knowledge assessment of service providers	X	O	O	O	O	O	O	X
Household survey	X	O	O	O	O	O	O	X
Data extraction	O	X	X	X	X	X	X	O
Community follow-up	O	X	X	X	X	X	X	O
Qualitative exploration	X	X	X	X	X	X	X	X

X – active data collection period for the specified activity, O – no data collection (activity not conducted during that time period

To ensure systematic monitoring of the implementation process, we will align the EMPIC activities with the WHO implementation research outcome variables (**Table 2**). This approach allows us to evaluate not only the outcomes of the intervention, but also how it is delivered and adopted within routine health system settings.

**Table 2 T2:** EMPIC process indicators and data collection by WHO implementation outcome

IR outcome	Definition	Measurement and data Source
Fidelity	Adherence to protocol for pneumonia classification and treatment, and referral for danger sign cases	Review of routine registers
Acceptability	Whether the enhanced management of pneumonia is accepted by caregivers, service providers, and health managers	Qualitative interviews and stakeholder consultations
Adoption	Initial uptake of enhanced pneumonia management by CHCPs	Qualitative interviews and routine register reviews
Coverage	Proportion of eligible children receiving enhanced management of pneumonia by month/quarter	Review of routine registers

CHCP – community healthcare provider

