### Study outcome

The primary outcome of interest is high (≥80%) and effective (patients receiving the full course of pneumonia treatment) coverage among under-five children (**Table 3**). The secondary outcome of interests are: treatment failure rate among young infants 7–59 days old with fast breathing and children 2–59 months old with chest indrawing and/or fast breathing pneumonia who received treatment from CCs; availability of essential commodities and supplies for managing childhood pneumonia; CHCPs’ knowledge of managing childhood pneumonia; caregiver’s knowledge and care-seeking practices regarding childhood pneumonia; and prevalence of pneumonia among under-five children, utilisation of CCs for pneumonia related symptoms; and treatment compliance.

**Table 3 T3:** Study enrolment and outcome assessment strategy

Activity	What	Who	When	Where	How
Case identification	Identify young infants with fast breathing pneumonia and children aged 2–59 months with fast breathing and/or chest indrawing pneumonia from data extracted from the service registers	Trained data extractors appointed by the study team	Twice in a week	Health facilities (CCs and union-level health facilities)	Trained data collectors will extract data from the registers or case record forms in the health facilities. From there, they will identify young infants with fast breathing pneumonia and children aged 2–59 months with fast breathing and/or chest indrawing pneumonia. They will provide this information to study-appointed nurses/paramedics who will conduct enrolment of the participants.
Screening and Enrolment	Enrol eligible young infants and children aged 2–59 months based on inclusion and exclusion criteria	Study appointed nurses or paramedics	One to three days after facility visit	Phone	Nurses and paramedics will screen the children based on the inclusion and exclusion criteria from the information received from study-appointed data extractors. They will contact the caregivers of the eligible children over the phone and take verbal consent for the home visit. They will enrol the children if consent is given by the caregivers.

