### Sample size and sampling strategy

#### Household survey

Baseline data from the Bangladesh Health and Demographic Survey 2017–18 indicate a 40% care-seeking rate among children under five with suspected pneumonia in the four weeks preceding the survey [39]. Assuming a baseline value of care-seeking practice for childhood illness among children under five years of age with suspected pneumonia in the past four weeks is 40% in baseline and (based on our objectives) 80% in end-line, and setting a 5% margin of error and 95% confidence interval, the unadjusted sample size is 23 children under five years of age with suspected pneumonia per district, increasing to 58 after adjustment for a 20% non-response rate and a design effect of 2.0. To achieve this sample size, we will need to reach 5121 households and 20 480 population per district. For the household survey, we will use a stratified sampling technique to ensure equal representation. Specifically, we will select villages, considered as the primary sampling unit, through probability proportional to size sampling, after which we will identify and interview all women with under-five children in the sampled villages.

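### The primary outcome is population-based effective coverage, but the assessment table it cites follows only children found in facility registers, and the household survey is not assigned to measure it

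*Protocol article*

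**What the plan says.** The opening of Methods gives the primary objective as raising access to pneumonia treatment "to achieve high (≥80%) and effective population-based coverage", where effective means that the full course is received. The Study outcome section restates it: "The primary outcome of interest is high (≥80%) and effective (patients receiving the full course of pneumonia treatment) coverage among under-five children". Its only pointer is to Table 3.

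Table 3 begins by identifying cases "from data extracted from the service registers" at community clinics and union-level facilities. Its other rows telephone the caregivers of those children for consent, extract the treatment they were given, and visit the enrolled children at home on days 7 and 14.

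Table 2, titled as process indicators, has a coverage row defined as "Proportion of eligible children receiving enhanced management of pneumonia by month/quarter", with "Review of routine registers" as its source.

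Under Activity 3, the baseline and endline household surveys are to cover caregivers' knowledge, "care-seeking practices, and treatment outcomes, defining treatment failure based on specific clinical criteria". The Household survey subsection sizes them on another quantity: "Assuming a baseline value of care-seeking practice for childhood illness among children under five years of age with suspected pneumonia", put at 40%, with 80% at endline. Every woman with a child under five in the selected villages is to be interviewed.

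The Data analysis section lists facility readiness, provider knowledge, clinic utilisation, compliance, treatment failure, caregiver knowledge and care-seeking. Coverage is not listed.

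**The concern.** A population-based proportion needs a denominator that includes sick children who never reach a provider. The stated assessment strategy has no such denominator. Table 3 starts from children who attended, and the Table 2 row is read from the same kind of register. The Table 2 row also counts children who receive enhanced management, not those who complete a course, so it differs from the primary outcome in the numerator as well. The one instrument that reaches non-attenders is not told to measure coverage.

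Non-attenders are not a small remainder here. The introduction says that only 46% of children with suspected pneumonia are taken to an appropriate provider, and that few of those with symptoms use public facilities. The findings are meant to inform scale-up. An 80% figure among children already in contact with a facility would answer a different question from the one the objective asks.

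**Working it through.** **1. The sources side by side.**

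- Objective (opening of Methods): population-based; full course received; at least 80%.
- Table 3, cited for the primary outcome: children in facility registers whose caregivers consent. No non-attenders.
- Table 2, coverage row: registers. Full course not part of the definition.
- Compliance (Data analysis): caregiver recall of antibiotics prescribed at community clinics, collected at follow-up. Attenders only.
- Household survey: population denominator, but full-course receipt is not named among its contents.
- Table 1: register extraction runs in Q1 to Q6 and not at baseline or endline. The household survey runs at baseline and endline. Registers therefore cannot show a baseline-to-endline change either.

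**2. What the survey was sized for.** Inputs from the Household survey subsection: 40% and 80% care-seeking, 95% confidence, 20% non-response, design effect 2.0. No power is stated, so 80% is assumed. For two proportions with pooled variance, two-sided:

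n = [1.96 × √(2 × 0.60 × 0.40) + 0.8416 × √(0.40 × 0.60 + 0.80 × 0.20)]² / (0.80 − 0.40)²

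= (1.358 + 0.532)² / 0.16 = 22.3, rounded up to 23.

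Adjusted: 23 × 2.0 / (1 − 0.20) = 57.5, rounded up to 58. Both stated figures, 23 and 58 per district, are reproduced. The survey size is therefore consistent with a before/after comparison of care-seeking. A ±5-point estimate of a single proportion would need 369 children at 40% or 246 at 80%, so the 5% margin mentioned in that subsection is not the precision this survey delivers.

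**3. How far a facility figure can sit from the population figure.** If a full course is obtained only through the care-seeking that is counted:

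population coverage = care-seeking × full-course share among those who seek care.

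The documents give no full-course share, so a range of 80% to 100% is assumed.

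- Care-seeking 40% (sizing baseline): 0.40 × 0.80 = 32% to 0.40 × 1.00 = 40%.
- Care-seeking 46% (introduction): 0.46 × 0.80 = 37% to 0.46 × 1.00 = 46%.

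In each case the figure among those who seek care is 80% to 100%.

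**4. What the planned survey would give for coverage.** Effective number per district: 58 × 0.80 / 2.0 = 23.2, about 23. At 80% coverage:

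- Per district: 1.96 × √(0.80 × 0.20 / 23) = 0.163, about ±16 points (Wilson interval 60% to 91%).
- Both districts, about 46 effective children: 1.96 × √(0.16 / 46) = 0.116, about ±12 points (Wilson interval 66% to 89%).

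For comparison, ±5 points at 80% would need 246 × 2.0 / 0.80 = 615 children per district.

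**The case against.** The strongest reply is that nothing says the primary result will come from registers. Table 2 already calls its contents process indicators, and its row speaks of eligible children without saying that they are attenders. A population survey is planned at both ends of the study, and its 80% endline value is said to follow from the objectives, which ties it loosely to the only 80% target. This is also a journal article, and survey items and denominators may sit in a full protocol or analysis plan that is not shown.

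Much of this stands. A reader might infer that the study will present attender coverage as population coverage. The text does not establish that, and it remains an inference. What the reply does not remove is the conflict inside the article: it does state an assessment strategy for the primary outcome, and that strategy is facility-based while the objective is population-based.

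Two other readings are tempting and should not be made.

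- That 80% care-seeking at endline puts the coverage target out of reach. It is an input for sizing a comparison and does not limit the care-seeking that may be achieved.
- That the theory-of-change sentence, "These primary outcomes are anticipated to translate into greater coverage", sets up rival endpoints. It describes links in a causal chain; the Study outcome section is where the endpoint is designated.

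A fair point also applies to the remedy. Caregiver-reported suspected pneumonia is not the group classified and treated at the clinic. It may include children with no pneumonia on assessment and children correctly referred. The fix below allows for this.

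**Conclusion.** The stated assessment strategy contradicts the stated primary objective, and the source and denominator of the primary outcome are not assigned. This goes beyond detail left to another document, because the pointer to Table 3 is itself wrong for a population-based outcome.

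The possible gap is large: 32% to 40% population coverage at 40% care-seeking, against 80% to 100% among those who seek care. That range rests on the assumed full-course share and on treating children outside counted care-seeking as not receiving a full course. It shows what the design would fail to detect and is not a forecast.

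The survey can supply the outcome at its present size, but only coarsely: about ±16 points per district and ±12 pooled at 80% coverage, using the plan's own design effect and non-response.

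**What to change.** - In Study outcome, name the baseline and endline household survey as the source of the primary outcome and replace the Table 3 pointer for that outcome. Table 3 can stay as the strategy for treatment failure and compliance.
- Denominator: all under-fives in sampled households with suspected pneumonia in the past four weeks. State that this caregiver-reported group is only a proxy for clinically classified pneumonia. Report children who were referred, or assessed as not having pneumonia, separately so that they are not counted as failures.
- Numerator: those reported to have received the full prescribed course. Ask this alongside the care-seeking items in both rounds.
- Say that the Table 2 row describes treatment among clinic attenders and is not the primary outcome.
- List effective coverage first in Data analysis.
- State the precision that the planned survey gives for coverage (about 23 effective children and ±16 points per district at 80%; about ±12 points pooled). Enlarging the survey is not required.

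The cost is a few added survey questions, reliance on caregiver recall, and a coverage figure that is less favourable and less precise than a register figure would be. The questions need to be settled before the baseline round, because the planned register extraction cannot supply a baseline value afterwards.
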